## Methods and design

### Study design

The overall study design is summarised in Figure 1. This study is registered with the Australian Clinical Trials Registry (ACTRNO12606000175572) and has been approved by the Human Research Ethics Committees of: The Children's Hospital at Westmead, Sydney West Area Health Service, and The University of Sydney.

**Figure 1 F1:**
[figure not shown]
**Study design**. ^a ^See additional file 1: Phase 1 of the Loozit^® ^group program – weekly topics and key content. ^b ^See additional file 2: Phase 2 of the Loozit^® ^group program – 'booster' session topics and key content

### Participants

#### Recruitment

Adolescents are being recruited in Sydney, Australia, via the media, schools, health professionals and several community organisations. The Children's Hospital at Westmead Public Relations department has contacted various media outlets and subsequently articles about the study have appeared in local and city-wide newspapers and, to a lesser extent, aired on television and radio programs. Local schools are approached with regards to placing information about the study in school newsletters, and school counselors are provided with information about the study. For some cohorts the study research assistants presented information at school meetings attended by staff, students, or parents and citizens. Health professionals working within the local area are informed about the study through faxes, flyers, e-mail bulletins and, less frequently, presentations are given. Other recruitment strategies include: placing flyers on notice boards in youth centers, local gyms and pharmacies; contacting local weight management businesses; contacting large businesses within the local area and asking them to include study information in their staff newsletters; and participants recommending the study to friends. For one cohort, flyers were distributed to households via a letter box drop in the local area of the community health centre at which the study was to be conducted.

#### Eligibility criteria

The inclusion and exclusion criteria for assessing adolescent eligibility to participate in the study (Table 1) are used during a telephone screen that is conducted with whoever enquires about the study (e.g. parents/carers, adolescents, health professionals or school counselors). Each enquiry about study participation is issued with a unique identification number that is used to distinguish individuals throughout the study. Adolescents who meet the study criteria are invited to an appointment with a research assistant, along with their parents/carers, in order to confirm eligibility based on objectively measured weight status. Informed consent or assent, depending on age, is obtained from adolescents who meet the study eligibility criteria and wish to participate. Consent is also obtained from one of the adolescent's parents/guardians. Although many adolescents are found to be ineligible during the telephone screen, it is uncommon for adolescents to be found ineligible at the appointment. Adolescents who are ineligible to participate, and their parents/carers, are encouraged to follow up with their general practitioner.

**Table 1 T1:** Inclusion and exclusion criteria for adolescent participation in the Loozit^® ^study

**Inclusion criteria**	**Exclusion criteria**
▪ Age 13.0–16.9 years	▪ Severely obese (i.e. BMI z-score^a ^>2.5) or if there is a secondary cause for overweight/obesity
▪ Overweight to moderately obese (i.e. BMI z-score^a ^range 1.0–2.5)	▪ Intellectual disability, significant medical illness, psychiatric disturbance
▪ Home access to a landline telephone	▪ Taking medications that affect weight status
▪ Home access to the internet to receive e-mails or access to a mobile phone to receive SMS messages	▪ Inability to take part in physical activity sessions
▪ Ability to attend the group program for 7 weeks in the first instance on the specified days^b^	▪ Poor level of spoken English (adolescent or parent/carer)
▪ At least one of the adolescent's parents/carers must be willing to also participate in the initial 7 parent group sessions	

^a ^calculated using Centers for Disease Control growth reference [41]

^b ^The 'G' and 'G +ATC' group programs are run on separate weeknights and therefore potential participants need to be available to attend on either evening, pending randomisation, even though they would only attend once per week

#### Randomisation

A computer generated randomisation sequence, stratified for sex, age group (13–14 years; 15–16 years), and intervention site was provided by staff in the Clinical Epidemiology Unit, The Children's Hospital at Westmead. The trial manager is responsible for concealed allocation which involves preparing, for each intervention site, sex and age group, a set of consecutively numbered opaque envelopes containing the group allocation 'G' or 'G+ATC'. After participant consent is obtained the next numbered envelope is opened by a research assistant (at the abovementioned appointment to confirm eligibility), revealing the group allocation and this is recorded along with the individuals pre-assigned identification number. Outcome assessors are the only persons blinded to group assignment.

#### Sample size

In adults, the clinical benefit of 5% relative weight loss is associated with improvements in HbA1c in Type 2 diabetes [33], blood pressure [34], total cholesterol and HDL cholesterol [35], and ovarian function in polycystic ovarian syndrome [36]. It could be reasonably assumed that adolescents will experience similar clinical benefits. Over a one year period, a clinically significant weight loss of 5% corresponds to a 0.4 unit change in BMI z-score, and a 5% reduction in waist circumference corresponds to a 0.2 unit reduction in waist circumference z-score. A sample size of 64 in each intervention arm will have 80% power to detect a 0.4 unit difference in mean change of BMI z-score from baseline to 2, 12 and 24 months follow-up in the two interventions (two group t-test, 0.05 two-tailed significance). Based on the results from our preliminary study, we have assumed the common SD is 0.8 for the change in BMI z-score, and that the calculated sample size is sufficient to detect a 0.2 unit change in waist circumference z-score, an 8% increase in HDL cholesterol, a 9% decrease in total cholesterol, a 7 mmHg and a 4 mmHg reduction in systolic and diastolic blood pressure, respectively, and a 15% increase in Harter global self-worth score [31]. To accommodate a 30% drop-out rate (based on adult studies), we aim to enrol 84 participants in each intervention arm.

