##### ii) Phase 1 – Adolescent and parent weekly group sessions

###### a) Format

Separate but simultaneous group sessions are held for adolescents and their parents/carers in the evening. Group sessions are facilitated by dietitians (but could be run by nurses or other health professionals) and each group typically has between five and nine members. Usually one parent/carer from each family attends but there are no restrictions on parent/carer numbers. Parents/carers are not permitted to bring younger children to the group sessions in order to minimise disruption. Due to budgetary constraints we are unable to provide child minding facilities for adolescent's siblings. The general structure of an adolescent and parent group session is outlined in Table 2.

**Table 2 T2:** Structure of weekly group sessions in phase 1 of the Loozit^® ^group program

**Adolescent session**	**Time** **(mins)**	**Parent session**	**Time** **(mins)**
i) Reconnect with group (includes an icebreaker) and review progress with goals	15	i) Reconnect with group and review progress with family goals	15
ii) Resistance activities	10	ii) Facilitator-led discussion on set topic^a^	50
iii) Facilitator-led discussion on set topic^a^	30	iii) Recap important points and record family goals for the week ahead	10
iv) Recap important points and record individual goals for the week ahead	10		
v) Fun active game and light refreshments	10		
Total	75	Total	75

^a ^See additional file 1: Phase 1 of the Loozit^® ^group program – weekly topics and key content

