###### b) Practical considerations

In order to preserve 'booster' group numbers when attrition occurrs, it was decided that groups allocated to the same study arm, from various cohorts that attended the same venue, should be combined. In order to prevent contamination between the two study arms, participants in the 'G' and 'G+ATC' interventions are never put together in the same group. This combining of groups in the maintenance phase also permits an informal peer support system where participants in the latter stages of the program provide an example and encouragement for participants in the early stages of phase 2.

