### Planned data analysis

Variables that are not normally distributed will be transformed to make them so, or non-parametric techniques will be used. Analysis of covariance will be used to test for differences in baseline characteristics by study arm and adjustment will be made to analyses as required. An estimation of intervention effect on outcome measures will be obtained at each follow-up observation (2, 12, & 24 months post-baseline) on an intention to treat basis. A mixed model will be used to test the average effect of the intervention after taking account of baseline covariates. A time-group interaction will be included to test whether the rate of change of BMI z-score is different between the 'G' and 'G+ATC' study arms. Planned contrasts will be used to measure between group differences at each evaluation time point. Randomisation should ensure distribution of ethnicity but ethnicity subgroup analysis and statistical adjustment will be made as required.

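### The 80% power for 64 per arm assumes independent participants, but treatment is delivered in arm-specific groups, so the stated power is too high at any positive within-group correlation.

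*Protocol article*

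**What the plan says.** All references are to the protocol article.

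- **Unit of randomisation.** Under Randomisation, individuals are allocated by numbered envelope, stratified by sex, age group and site.
- **Delivery.** Under Phase 1, Format, "each group typically has between five and nine members". Table 1, note b, puts the two arms on different evenings. Under Phase 2, Practical considerations, booster groups from different cohorts at one venue are combined within an arm, and "participants in the 'G' and 'G+ATC' interventions are never put together in the same group".
- **Sample size.** "A sample size of 64 in each intervention arm will have 80% power" "to detect a 0.4 unit difference in mean change of BMI z-score", with the basis given as "two group t-test, 0.05 two-tailed significance". On variability: "we have assumed the common SD is 0.8 for the change in BMI z-score". On attrition: "To accommodate a 30% drop-out rate (based on adult studies), we aim to enrol 84 participants in each intervention arm". No ICC or design effect appears.
- **Analysis.** Under Planned data analysis, "A mixed model will be used to test the average effect of the intervention after taking account of baseline covariates". A time-by-group interaction and planned contrasts follow. There, group means study arm. No session-group, facilitator or site effect is named, and no random-effects structure is given.

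**The concern.** Members of one session group share peers, an evening and a facilitator, and the protocol wants them to influence each other. The Content and Goal setting sections describe sessions built around interaction and mutual support, and the phase 2 merging is said to create informal peer support. Some within-group correlation in outcome is therefore to be expected.

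Each group belongs wholly to one arm, so variation between groups adds to the variance of the arm difference. A power figure that assumes independent participants leaves this out. An analysis that also left it out would give standard errors that are too small for the comparison of G+ATC with G, which is the question that randomisation addresses (hypothesis 2).

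**Working it through.** **Inputs from the Sample size section:** difference 0.4, SD 0.8, two-sided alpha 0.05, 64 analysed and 84 enrolled per arm.

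**Input from Phase 1, Format:** five to nine members per group, midpoint 7.

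**Assumption:** the ICC is not in the document; the range 0.01 to 0.10 is assumed.

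**1. Reproduce the stated figure.** The standardised effect is 0.4 / 0.8 = 0.5. The exact two-group t-test calculation needs 63.8 per arm, rounded up to 64, with power 80.1% at 64. No design effect is hidden in the number.

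**2. Group size among those analysed.** Groups of 7 describe those enrolled: 84 / 7 = 12 groups per arm. Power is quoted for 64 analysed, so the relevant mean size is m = 64 / 12 = 5.33. This assumes that losses spread over all the groups and that none disappears.

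**3. Formulas.**
- Design effect: DE = 1 + (m − 1) × ICC = 1 + 4.33 × ICC
- Effective number per arm: 64 / DE
- Power: noncentral t with 126 degrees of freedom and noncentrality 0.5 × √(64 / (2 × DE))
- Type I error if groups are ignored in the model: 2 × [1 − Φ(1.96 / √DE)]

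| Assumed ICC | DE | Effective n per arm | Power | Type I error if no group term |
|---|---|---|---|---|
| 0 | 1.00 | 64.0 | 80.1% | 5.0% |
| 0.01 | 1.043 | 61.3 | 78% | 5.5% |
| 0.02 | 1.087 | 58.9 | 77% | 6.0% |
| 0.05 | 1.217 | 52.6 | 72% | 7.6% |
| 0.10 | 1.433 | 44.7 | 65% | 10.2% |

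**4. Worked row, ICC 0.05.** DE = 1 + 4.33 × 0.05 = 1.217. Effective n = 64 / 1.217 = 52.6. Noncentrality = 0.5 × √(52.6 / 2) = 2.56, giving power 72%. If groups are ignored, the true standard error is √1.217 = 1.10 times the model's; 1.96 / 1.10 = 1.78, a two-sided error of 7.6%.

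**5. Merged booster groups (illustration).** If phase 1 groups merged in pairs, m = 2 × 5.33 = 10.67. At ICC 0.05, DE = 1 + 9.67 × 0.05 = 1.48 and power is about 63%. The number of groups combined is not stated, and the ICC in a merged group need not equal that in a phase 1 group, so this shows direction only.

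**The case against.** **The analysis half rests on silence.** A reader might infer that the analysis treats participants as independent and that its standard errors are too small. The article does not support that. It says only that a mixed model will be used and names no random effect at all, not even for participant, so the absence of a group term does not show that one was excluded. A journal article commonly leaves such detail to a fuller plan. This objection stands: the type I figures are conditional. It does not touch the power statement, which is a stated figure from a named test. A group term added elsewhere would not make 80% correct.

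**Facilitators.** A reader might also infer that a facilitator effect could pass for an effect of the additional contact. The article does not say that facilitators differ by arm; separate evenings allow one facilitator to serve both. Standardised training, a scripted manual and weekly meetings (Staff training) are meant to limit such variation. A facilitator effect is only a possibility. Peer group and evening remain nested in arm either way.

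**Not all shared variation reaches the arm contrast.** Randomisation is stratified by site, so site-level differences are largely balanced. This stands, and it argues against a high ICC.

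**The loss may be small.** At an ICC of 0.01 to 0.02 power falls by only about 2 to 3 points, and nothing in the document favours the upper part of the range. The fixed phase 1 group meets for seven weekly sessions only, and the extra contact under test is given individually by telephone and message. These points limit the size. Against them, the between-arm hypothesis concerns 12 and 24 months, when merged groups may be larger than those in phase 1.

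**Conclusion.** The point holds for the power statement. Sixty-four per arm is exactly the independent-participant figure, and delivery is in arm-specific groups with intended peer influence, so true power is below 80% at any positive ICC. Under the assumed range it lies between about 78% and 65%. This rests on an ICC the document does not give and on about 12 groups per arm with 5.3 analysed members each.

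For the analysis, the conclusion is conditional. If the mixed model has no therapy-group term, the nominal 5% arm contrast runs at about 5.5% to 10.2%. The article neither includes nor excludes such a term. It does not establish inflated error as a fact, nor that a facilitator effect would be mistaken for a treatment effect.

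The change should be made because it is cheap and protects the main randomised comparison. At a low ICC its practical effect will be minor.

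**What to change.** **Analysis.** In the mixed model for follow-up outcomes with baseline as a covariate, include a random effect for the phase 1 therapy group. If baseline is instead part of the outcome vector, use a group-by-time random effect, because a constant group intercept cancels from change and leaves the clustering of change uncorrected. Use small-sample degrees of freedom such as Kenward-Roger. Repeat the analysis with the merged booster group as the cluster, as a sensitivity analysis.

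**Sample size statement.** Restate power with a design effect over a stated ICC range, using the group size expected among those analysed. Do not enrol more participants on this account.

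**Cost.** No new data collection should be needed, since facilitators already record attendance for each session (Evaluation of group sessions). Randomisation and delivery are unchanged. The merged groups overlap the phase 1 groups, so the sensitivity analysis needs a second group identifier. Confidence intervals become slightly wider and the stated power lower. As a cautious limit, with group-based degrees of freedom of 2 × (12 − 1) = 22 in place of 126, the power in the table becomes about 75%, 74%, 69% and 62% at ICC 0.01, 0.02, 0.05 and 0.10.

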**Methods and design:**

The study design is a two-arm randomised controlled trial that aims to recruit 168 overweight and obese 13–16 year olds (Body Mass Index z-score 1.0 to 2.5) in Sydney, Australia. Adolescents with secondary causes of obesity or significant medical illness are excluded. Participants are recruited via schools, media coverage, health professionals and several community organisations. Study arm one receives the Loozit^® ^group weight management program (G). Study arm two receives the same Loozit^® ^group weight management program plus additional therapeutic contact (G+ATC). The 'G' intervention consists of two phases. Phase 1 involves seven weekly group sessions held separately for adolescents and their parents. This is followed by phase 2 that involves a further seven group sessions held regularly, for adolescents only, until two years follow-up. Additional therapeutic contact is provided to adolescents in the 'G+ATC' study arm approximately once per fortnight during phase 2 only. Outcome measurements are assessed at 2, 12 and 24 months post-baseline and include: BMI z-score, waist z-score, metabolic profile indicators, physical activity, sedentary behaviour, eating patterns, and psychosocial well-being.

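### Enrolling 84 per arm does not cover 30% drop-out from the required 64: about 59 would remain, with about 77% power instead of 80%

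*Protocol article*

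**What the plan says.** All the inputs are in the Sample size section of the protocol article. The evaluable number comes first: "A sample size of 64 in each intervention arm will have 80% power". The effect that this power refers to is a 0.4-unit difference between arms in the change in BMI z-score at the three follow-up visits. The test is given as "two group t-test, 0.05 two-tailed significance", and for the variability "we have assumed the common SD is 0.8 for the change in BMI z-score". The section then moves from the evaluable number to the number enrolled: "To accommodate a 30% drop-out rate (based on adult studies), we aim to enrol 84 participants in each intervention arm". The abstract (Methods and design) carries the doubled figure forward as the recruitment target, describing a "two-arm randomised controlled trial that aims to recruit 168 overweight and obese 13–16 year olds".

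The article does not show the formula that takes 64 to 84.

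**The concern.** A drop-out rate is ordinarily the share of enrolled participants who are lost. To end with n evaluable after losing a share d, one enrols n/(1 − d). Multiplying n by (1 + d) falls short, because the loss applies to the larger enrolled number and not to n. The figure of 84 looks like the second calculation.

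This is the only power calculation in the article, and BMI z-score is one of its two primary outcomes. The 64 per arm has almost no slack, so any shortfall takes power below 80%. The same section also relies on this sample size for waist circumference z-score, cholesterol, blood pressure and self-worth. If the sponsor's own drop-out assumption came true over two years, a null result could be read as coming from a trial with 80% power when the stated calculation no longer supports that.

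**Working it through.** **Inputs (all from Sample size):** difference δ = 0.4; SD of change σ = 0.8; two-group t-test, two-sided α = 0.05; 64 evaluable per arm; drop-out d = 0.30; 84 enrolled per arm.

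**Step 1: reproduce the 64.** With n per arm, the non-centrality parameter is δ / (σ√(2/n)) on 2n − 2 degrees of freedom. Power is the probability that the non-central t exceeds the two-sided 5% critical value.

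- n = 64: 0.4 / (0.8 × √(2/64)) = 2.83, power 80.1%.
- n = 63: power 79.5%.

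The exact requirement is 63.8, so 64 is right and is the smallest whole number that reaches 80%.

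**Step 2: try to reproduce the 84.**

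| Route from 64 | Result | Rounded up |
|---|---|---|
| n/(1 − d) = 64/0.70 | 91.4 | 92 |
| n × (1 + d) = 64 × 1.3 | 83.2 | 84 |

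Only the second route gives the printed figure. Starting from 63 (the normal-approximation answer) gives 63/0.70 = 90 or 63 × 1.3 = 81.9, rounded up to 82. Neither is 84.

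**Step 3: what 84 per arm delivers at 30% loss.** Completers per arm: 84 × 0.70 = 58.8.

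| Completers per arm | Power, non-central t | Power, normal approximation |
|---|---|---|
| 58 | 76.1% | 76.8% |
| 58.8 | 76.7% | 77.4% |
| 59 | 76.8% | 77.5% |
| 64 | 80.1% | 80.7% |

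Difference detectable with 80% power at 58.8 per arm: 0.40 × √(63.8/58.8) = 0.417.

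**Step 4: the drop-out that 84 does cover.** 1 − 64/84 = 0.238, so 64 remain only if drop-out is at most 23.8%.

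**Step 5: the enrolment that 30% would need.** 92 per arm leaves 92 × 0.70 = 64.4 completers, which restores 80%. In total that is 184 instead of 168, or 16 more participants (16/168 = 9.5%).

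**The case against.** The arithmetic itself is hard to dispute. The serious objections concern how much it matters and how far the 77% applies.

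- **The effect is small against the uncertainty of the inputs.** The SD comes from a pilot that the article itself calls underpowered, and the 30% comes from adult studies. At 58.8 per arm, 80% power returns if the SD is 0.8 × √(58.8/63.8) = 0.768, a 4% change. This is true and limits the practical effect. It does not make 84 the right answer to the stated inputs.
- **The planned analysis is not a t-test on completers.** The Planned data analysis section specifies intention to treat and a mixed model with baseline covariates. That model can use the earlier visits of participants who later leave, and adjustment may reduce residual variance. Some power may be recovered, but the article gives nothing from which to quantify it. The sample size section rests on a t-test and takes no credit for such gains. By adding a drop-out allowance it also treats those who leave as lost.
- **The 30% is not tied to a visit.** If it is the cumulative loss at 24 months, fewer will be missing at 2 and 12 months, and any visit with loss of 23.8% or less still has 64 per arm. With no loss at all, power at 84 per arm is about 90%. This stands: the 77% describes a visit at which 30% are already missing.
- **The multiplication by 1.3 is inferred.** This also stands. The match is exact after rounding up, but the conclusion does not need it: however 84 was reached, it does not leave 64 after 30% loss.
- **The article attaches 80% to the 64, not to the 84.** That is literally so, but enrolling 84 to accommodate the drop-out can only mean that the 64 is to be preserved.

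**Conclusion.** The point holds. The 64 per arm is correct; the step to 84 is not. The required number, the drop-out rate and the enrolment target cannot all be right together. At 30% drop-out the trial has about 59 per arm. Power for a 0.4-unit difference is then about 77%, some 3 points below the stated level, and the difference detectable with 80% power is about 0.42.

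These sizes assume the section's own SD of 0.8, its two-group t-test, drop-out counted as a share of those enrolled, and a visit at which the full 30% are missing. The loss is modest and affects no estimate or error rate. It is nevertheless a wrong figure, and the recruitment target depends on it.

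**What to change.** Correct the last sentence of the Sample size section. Any one of these is consistent:

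1. Keep 84 per arm and state that this retains 64 per arm if drop-out is at most about 24%.
2. Keep 84 per arm and the 30%, and state that about 59 per arm would then remain, giving about 77% power for a 0.4-unit difference (80% power for about 0.42).
3. Keep both the 30% and the 80%, and raise the target to 92 per arm, 184 in total. The abstract's 168 then changes too.

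Options 1 and 2 cost one sentence and no extra participants; the stated power or the tolerated drop-out becomes slightly less favourable. Option 3 costs 16 more participants. As recruitment began in May 2006 according to the Time plan, restating the figures at 168 is the cheaper course. Whichever is chosen, the sentence should also say at which follow-up visit the drop-out is assumed.
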